| **Research Protocol Title:** Role of L-Carnitine supplementation on rate of weight gain and biomarkers of Environmental Enteric Dysfunction (EED) in children with severe acute malnutrition |
| Proposed start date: 01/09/2021 Estimated end date: 31/08/2023 |
| **Background (brief):**   1. **Burden:**   Globally, an estimated 14.3 million under-5 children are severely malnourished. Two-thirds of them live in Asian countries including Bangladesh. Acute malnutrition is an underlying cause of nearly half of global deaths in under-5 children despite standardized rehabilitation protocols. It is also associated with high relapse rates following discharge.   1. **Knowledge Gap:**   Malnourished children suffer from deficiencies of several essential nutrients. Studies showed that malnourished children had lower serum carnitine level and demonstrated its role on the rate of weight gain in children with severe acute malnutrition (SAM). The consequences of nutritional impairment can be perilous if carnitine deficiency is coupled with Environmental Enteric Dysfunction (EED). Recent evidence confirms that EED is characterized by secondary carnitine deficiency in children. Carnitine deficiency leading to EED may cause childhood growth faltering and impaired cognitive development. However, evidence on carnitine status and its consequences in relation to EED in diarrheal children with SAM is very limited in Bangladesh.   1. **Relevance:**   Such lack of information regarding the role of L-carnitine in improving the rate of weight gain in malnourished children susceptible to EED is an obstacle in limiting the relapse and adverse consequences of SAM in diarrheal children living in resource limited countries.  **Hypothesis:** L- carnitine supplementation for 15 days in children with SAM will improve the rate of weight gain and biomarkers of EED  **Objective:** To investigate the role of L-carnitine supplementation on the rate of weight gain, duration of hospital stays and EED biomarkers among children with severe acute malnutrition  **Methods:** This study will be a double-blinded, placebo-controlled randomized clinical trial where the children in intervention arm will receive L-carnitine supplementation for 15 days. The control arm will receive placebo for the same duration. We will enroll diarrheal children aged 9-24 months suffering from SAM both in intervention and control groups. This study will be conducted at Dhaka Hospital of icddr,b.  **Outcome measures/variables:**   - Primary outcome variable: Rate of weight gain - Secondary outcome variables:   1. Duration of hospital stays  2. EED biomarkers [myeloperoxidase (MPO), neopterin (NEO), alpha-1 anti-trypsin (A1AT), kynurenine: tryptophan (KT) ratio, and citrulline] |

**Description of the Research Project**

## Hypothesis to be tested:

| In a hypothesis testing research proposal, briefly mention the hypothesis to be tested and provide the scientific basis of the hypothesis, critically examining the observations leading to the formulation of the hypothesis. |
| --- |

Does this research proposal involve testing of hypothesis:  No Yes (describe below)

L-carnitine supplementation for 15 days in children with severe acute malnutrition will improve the rate of weight gain and biomarkers of EED

## Specific Objectives:

| Describe the specific objectives of the proposed study. State the specific parameters, gender aspects, biological functions, rates, and processes that will be assessed by specific methods. |
| --- |

## To investigate the role of L-carnitine supplementation on the rate of weight gain among the children with SAM

## To investigate the role of L-carnitine supplementation on the duration of the hospital stays

## To examine the role of L-carnitine supplementation on EED biomarkers, for instance, myeloperoxidase (MPO), neopterin (NEO), alpha-1 anti-trypsin (A1AT), kynurenine: tryptophan (KT) ratio, and citrulline in children with SAM

## Background of the Project including Preliminary Observations:

| Provide scientific validity of the hypothesis based on background information of the proposed study and discuss previous works on the research topic, including information on sex, gender and diversity (ethnicity, SES) by citing specific references. Critically analyze available knowledge and discuss the questions and gaps in the knowledge that need to be filled to achieve the proposed aims. If there is no sufficient information on the subject, indicate the need to develop new knowledge. |
| --- |

Carnitine is a low molecular weight naturally occurring compound, found in all mammalian species (1, 2). L-carnitine (levocarnitine; 3-hydroxy-4-N-trimethylammonium butyrate) is a standard biologically active form of carnitine (1, 2). It is one of the essential nutrients that plays a critical role in the β-oxidation of fatty acids and energy production in the form of adenosine triphosphate (ATP) (3-5). Carnitine is important for the improvement of heart and brain function, muscle movement, and many other body processes as well as disease prevention (3, 4). It is synthesized in the liver, kidney, and brain from essential amino acids lysine and methionine (4, 6). It is found mainly in animal-source foods, such as red meat, chicken, fish, and dairy products, whereas only a negligible amount is available in plant source foods (4). In normal individuals, the homeostasis is achieved and maintained by a combination of oral absorption from dietary sources, *de novo* biosynthesis, carrier-mediated distribution into tissues, and renal tubular reabsorption (4). Free carnitine is filtered by renal glomeruli and is 97% reabsorbed by the kidney tubules (7). Earlier studies suggest that malnourished children had lower serum carnitine, particularly among those with severe acute malnutrition (3, 5).

[figure not shown]

**(Source URL:** [**https://www.youtube.com/watch?v=C-k_Ehv0jbs**](https://www.youtube.com/watch?v=C-k_Ehv0jbs)**)**

**Figure 1: The Carnitine Shuttle**

Globally the rates of severe acute malnutrition (SAM) remain alarming and an estimated 14.3 million under-5 children are severely malnourished (8). Malnutrition is an underlying cause of nearly half of global deaths in under 5 children despite standardized rehabilitation protocols (8-10). It is associated with high relapse rates following discharge. The management of SAM occupies a unique position between clinical medicine and public health, and its management requires special attention (11). Recent trend shows that two-thirds of the children with SAM live in Asian countries including Bangladesh (8). The latest national survey of Bangladesh (BDHS 2017-18) shows that 31% of under-5 children were stunted (height for length z score), 9% were severely stunted, 22% were underweight (WAZ), 4% were severely underweight, 8% were wasted (Weight for Length z score) and 2% were severely wasted (12). The figures demonstrate that the burden of childhood malnutrition is still substantial in Bangladesh. It is reported earlier that malnourished children suffer from deficiencies of several essential nutrients, and carnitine is one of those essential nutrients. Past evidence also suggests that malnourished children suffer from carnitine deficiency, and it may afflict the growth and development of a children of growing age.

Carnitine deficiency may occur due to genetically determined metabolic disorders, acquired medical conditions, and some other external factors such as inadequate intake of carnitine, and decreased biosynthesis of carnitine (13-16). It is noted that the main features of carnitine deficiency are similar to the manifestation of mitochondrial insufficiency, for example, fatigue, muscle weakness, and hypotonia, slackness, drowsiness or irritability physical retardation, failure to thrive, recurrent infection, cardiovascular disorder, hypoglycemia, hyper ammonia, decrease school performance, etc. (17). Few studies showed carnitine has a role in the rate of weight gain in malnourished children (5). A positive correlation between albumin and plasma carnitine levels in PEM has also been reported (5). An incremental growth was observed in 22 out of 33 carnitine-administered patients who presented with failure to thrive (17) and this was attributed to the role of carnitine as a muscle growth factor. Carnitine helps in energy production in the form of ATP. Several studies found that ATP has beneficial effects on nutritional status (18). Therefore, it is assumed that carnitine may help in increasing weight gain by increasing the ATP production.

Recent evidence confirms that Environmental Enteric Dysfunction (EED), an asymptomatic small intestinal disorder, is characterized by secondary carnitine deficiency in children aged <60 months (19). EED is also characterized by small intestinal inflammation and abnormal gut permeability due to generalized disturbances of small intestinal structure and function. The histopathological features of EED includes blunting or atrophy of intestinal villi, increased inflammatory infiltrates in lamina propria, and hyperplasia of small intestinal crypts (20, 21). However, a number of fecal and blood biomarkers have been proposed to determine EED in low-income settings, for example, MPO, NEO, A1AT, KT ratio, and Citrulline. EED is an acquired condition and caused by repeated enteropathogen infections which damage the gut structure and results in impaired nutrient absorption (22, 23). This sub-clinical condition is pervasive in the under five children living in tropical countries. EED is found to be an emerging contributor of childhood growth faltering (24). However, the exact pathogenesis and metabolic consequences of EED are not well understood. Recent documents linking between EED and carnitine deficiency provides signals regarding role of carnitine deficiency and EED in childhood malnutrition. It is assumed that carnitine deficiency leading to EED may negatively affect the physical growth and cognitive development of young children (19). It is also possible that consequences of severe malnutrition can be perilous in young children if carnitine deficiency is coupled with EED (19). Nevertheless, evidence of carnitine status in diarrheal children with SAM is very limited in Bangladesh (5). The role of treatment of SAM in the improvement of carnitine status among malnourished children is not well known (5). As well as EED is pervasively common among children in the country. There may have specific biological obstacles concerning EED which render nutritional therapy ineffective or partially effective in children with SAM. The impact of L-carnitine supplementation on biomarkers of EED among malnourished children is also unknown, albeit EED can be ameliorated by L-carnitine supplementation as it is linked to carnitine deficiency. Therefore, we are proposing this study to assess carnitine level and explore its role on the rate of weight gain (anthropometric measurements), duration of hospital stays, and biomarkers of EED in severely malnourished children in Bangladesh.

## Research Design and Methods

| Describe the research design and methods and procedures to be used in achieving the specific aims of the research project. If applicable, mention the type of personal protective equipment (PPE), use of aerosol confinement, and the need for the use BSL2 or BSL3 laboratory for different part of the intended research in the methods.. Define the study population with inclusion and exclusion criteria, the sampling design, list the important outcome and exposure variables, describe the data collection methods/tools, and include any follow-up plans if applicable. Justify the scientific validity of the methodological approach (biomedical, social, gender, or environmental).  Also, discuss the limitations and difficulties of the proposed procedures and sufficiently justify the use of them. |
| --- |

**Study Design**

This study will be a double-blinded, placebo-controlled randomized clinical trial where the children in intervention arm will receive L-carnitine supplementation for 15 days. The control arm will receive placebo for the same duration. We will enroll diarrheal children with SAM both in intervention and control groups. In this study, SAM would be considered if WLZ/WHZ is <-3 SD of WHO child growth standards or clinical signs of bilateral pedal edema are present, or the mid-upper arm circumference (MUAC) is <115 mm.

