**Figure 3: Block Randomization**

| Criteria |  | Male | | Female | |
| --- | --- | --- | --- | --- | --- |
| WLZ score ≤3SD, or/and  MUAC <115 mm | Block Size 4 | AABB | BBAA | ABAB | BABA |
| Block Size 6 | AAABBB | BBBAAA | ABABAB | BABABA |
| Block Size 8 | AAAABBBB | BBBBAAAA | ABABABAB | BABABABA |
| Block Size 10 | ABABABABAB | | | |
| Bilateral Pedal Edema | Block Size 4 | AABB | BBAA | ABAB | BABA |

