**Anthropometric measurements**

All the measurements (length, weight, MUAC) will be taken at enrolment and on each day when the participants will receive intervention/placebo. If not possible, a one-day window period will be used. End-line anthropometry data will be collected on the 15th day of supplementation. In addition, we will measure anthropometry on the 180th day after the completion of supplementation to observe the long-term effect of the intervention on the rate of weight gain. Trained staff will take all the measurements as per the standard operating procedures (SOPs) and keep records in standard CRFs. Every measurement will be taken twice and the average will be documented. The Seca weighing scale will be used for weight measurement and Seca length board will be used for length measurement. To ensure the quality of anthropometric data, 5% of the participants will be measured second time within 24 hours of each data collection. Additionally, quality control assessment will be organized monthly and inter-rater reliability will be calculated to ensure the anthropometric data quality. Steps will be taken to minimize the discomfort and inconvenience of the participants during the anthropometric measurement.

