**Management**

Children will be given their first dose of supplementation when they would be considered improved, i.e. no diarrhea for last 24 hours, patient fulfill the criteria of NRU transfer (presence of oedema, or/and WLZ <-3SD, or/and WAZ <-4SD). At NRU after randomization trained research staff will observe each child for 60 minutes following ingestion of investigational product and record any adverse event- nausea, vomiting etc. Vomiting is defined as the forceful emptying of stomach contents and will be recorded if it happened within 60 minutes following the administration of investigational product. Children will get supplementation of investigational product in addition to standard of care at NRU for 15 days. Supplementation will be given at every 8 hours under supervision of a trained staff.

**Study Days**Patients will be followed up every day by a study physician at NRU for 15 days. Adverse events will be documented and drug accountability recorded. During this intervention period if study participants fulfill the discharge criteria of NRU (WLZ/WHZ ≥ -2SD, WAZ ≥ -3SD and oedema resolved), we will discharge the patient with remaining dose of the syrup and advise them to come for follow up into after completion of the remaining dose. This same method will be applicable for both the intervention arm and placebo arm.

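### Oedema at enrolment has its own randomisation blocks, but the unadjusted primary comparison of weight gain ignores it

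*Protocol*

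**What the plan says.** **Who enters.** Under Study Design, low weight-for-length, low arm circumference, "or clinical signs of bilateral pedal edema are present" each suffices for severe acute malnutrition. Oedema is not among the exclusion criteria.

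**When dosing starts.** Under Management, the first dose follows transfer to the nutritional rehabilitation unit (NRU), and the transfer criteria are "presence of oedema, or/and WLZ <-3SD, or/and WAZ <-4SD". A child can therefore be oedematous at the first dose.

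**When oedema should be gone.** The NRU discharge criteria include "WAZ ≥ -3SD and oedema resolved", and the protocol provides for discharge before the 15 days are complete.

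**What is measured.** Under Anthropometric measurements: "All the measurements (length, weight, MUAC) will be taken at enrolment and on each day when the participants will receive intervention/placebo". Also: "End-line anthropometry data will be collected on the 15th day of supplementation". The primary outcome is listed only as rate of weight gain. The reply to the Research Review Committee says that the difference will be measured after 15 days of supplementation.

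**How children are allocated.** Figure 3 (Block Randomization) has a separate row, "Bilateral Pedal Edema", with two blocks of 4 for boys and two for girls. An alternative description follows the word Or. It uses permuted blocks of varying size and names no strata.

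**How the outcome is analysed.** Data Analysis gives t-tests for numeric variables and the Mann-Whitney test for nonparametric continuous data, described as bivariate, crude analyses. It names no term, stratum or subset for oedema.

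**The concern.** As oedema clears, a child loses weight while recovering. Over 15 days, the recorded change is tissue gained minus fluid lost. In a child without oedema it is tissue alone. The same number therefore means different things in the two groups, and their average gains probably differ.

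The block table shows that the investigators regard oedema as important enough to balance between arms, yet the stated analysis makes no use of it. In an unadjusted test, any difference in mean gain between oedematous and other children goes into the residual variance and widens the confidence interval for the treatment effect. With about 44 evaluable children per arm there is little precision to spare. If the blocks in Figure 3 are used, the arms are balanced on oedema by design, but the t-test's standard error does not take credit for that. If the alternative scheme is used, chance imbalance in oedema is possible and the analysis does not correct for it.

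There is also a question of interpretation. Resolution of oedema helps a child qualify for discharge, and so bears on the secondary outcome of hospital stay, while the fluid lost lowers the primary outcome. Without a result for children free of oedema, the reader cannot tell how far a pooled difference in weight gain reflects tissue.

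**Working it through.** **1. Inputs.** From Sample Size Calculation: SD 4.3, difference 2.4, margin 0.1, quantiles 1.645 and 0.845, 10% attrition. From Randomization and Figure 3: the block counts. The shortfall in oedematous children is not in the protocol and is assumed below.

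**2. The plan's own sample size.** n = 2 × ((1.645 + 0.845)/(2.4 − 0.1))² × 4.3² = 43.3, so 44 per arm. With attrition, 44/0.9 = 48.9, so 49 per arm. The stated 49 reproduces.

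**3. Share with oedema.** The block plan sums to 8×4 + 4×6 + 4×8 + 1×10 = 98. The oedema row is 4×4 = 16, so p = 16/98 = 0.163. This is the number of places in the table, not an expected prevalence.

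**4. Added variance.** Let oedematous children gain on average D less than the others, with the same SD of 4.3 within each group. The variance of the pooled outcome is

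4.3² + p(1 − p)D², with 4.3² = 18.49 and p(1 − p) = 0.163 × 0.837 = 0.1366.

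| Assumed D (outcome's units) | Added variance | Total | Increase | SD |
|---|---|---|---|---|
| 3 | 1.23 | 19.72 | 6.6% | 4.44 |
| 5 | 3.42 | 21.91 | 18.5% | 4.68 |
| 7 | 6.69 | 25.18 | 36.2% | 5.02 |

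A term for oedema at enrolment removes this component from the residual.

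**5. What that means for power.** On the plan's own basis (one-sided 1.645, difference 2.3, 44 per arm), power = Φ(2.3/(SD × √(2/44)) − 1.645). With SD 4.3 this is Φ(2.509 − 1.645) = 80.6%. With the SDs in the table it is 78.4%, 74.5% and 69.3%. These figures treat oedema as unbalanced by design. If the Figure 3 blocks are used, the loss is somewhat smaller, because the estimate itself varies less than the unadjusted standard error implies.

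**6. Could oedema reverse the result?** Suppose fluid loss by day 15 differed between arms by 3 to 7 units among oedematous children. The overall difference would move by 0.163 × 3 = 0.49 to 0.163 × 7 = 1.14. Cancelling a true difference of 2.4 would need 2.4/0.163 = 14.7 units. If the unit is g/kg/day, that is 14.7 × 15/1000, about 22% of body weight.

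**The case against.** Several stronger readings are tempting, and the protocol does not support them.

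- **That the protocol fixes enrolment weight as the start.** A reader may infer this from the measurement schedule and from a phrase about gain from baseline in the reply to the Research Review Committee. That phrase answers a question about the unit of the 2.4, which comes from a cited study. No sentence defines the start, and weights are planned on every dosing day.
- **That a product which speeds oedema clearance would look harmful.** If oedema has cleared in both arms by day 15, each child has lost the fluid whatever the speed. Only a difference between arms in clearance still present at day 15 would count against the product. Step 6 shows that such a difference would have to be very large to cancel the planned effect.
- **That the planning SD is too small.** The protocol does not say whether the population behind 4.3 included oedematous children. If it did, the added variance is partly or wholly counted already.
- **That the comparison is biased.** Randomisation protects it. The issue is precision and interpretation.

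It can also be said that covariates belong in the statistical analysis plan, which is not shown. That would answer a protocol silent on the method. This one states a crude comparison. In Appendix 1 an external reviewer asked for an adjusted model with its covariates described; the reply offers thanks only, and Data Analysis contains no such model.

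Two doubts about the figures stand. The share of 16/98 comes from a table followed by an alternative without strata. The size of the shortfall is assumed, and its unit is as unclear as that of 2.4 and 4.3, which the protocol describes only by saying that weight was measured in kg.

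**Conclusion.** The point holds as a weakness of the stated primary analysis. The protocol admits oedematous children, allows dosing while oedema is present, expects it to resolve and gives it its own blocks. It then leaves it out of the comparison. That gives up precision at no gain and leaves the pooled result harder to interpret.

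The size is uncertain. The illustration of 7%, 18% or 36% more variance rests on three assumptions: 4.3 is the SD in children without oedema, 16/98 of children are oedematous, and their mean shortfall is 3, 5 or 7. If few oedematous children enrol, or the shortfall is small, the loss is slight. The case for the change does not depend on these figures, because adjusting for a baseline factor already used in allocation keeps the randomised comparison and costs almost nothing.

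**What to change.** In Data Analysis, replace the unadjusted primary comparison with a linear model of the day-15 rate of weight gain on arm, adjusted for oedema at enrolment (yes/no) and for sex, the other factor in Figure 3. Report the adjusted difference with its confidence interval.

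State that enrolment weight is the start for all children. This closes the gap in the outcome definition and keeps the start at randomisation.

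Pre-state a sensitivity analysis in children without oedema at enrolment. An analysis that starts at the first oedema-free weight should be at most a secondary sensitivity analysis. That start comes after randomisation, treatment may affect it, it gives children different measurement windows, and it is undefined where oedema does not clear.

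Say which of the two randomisation descriptions applies. Keep the adjustment under either.

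The cost is a few sentences. Oedema at enrolment is already needed to establish eligibility, and the weights are already planned. Daily oedema status would be needed only for the optional secondary analysis; the text available does not show whether the case record form collects it.
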